## Abstract

**Background:**

Malnutrition is a common and serious complication among patients undergoing peritoneal dialysis (PD), leading to poor clinical outcomes, reduced quality of life, and increased mortality. Although current renal dietary guidelines emphasize adequate protein intake, they are predominantly animal based and may exacerbate inflammation and metabolic complications. Emerging evidence suggests that plant-focused diets can improve nutritional and inflammatory profiles without raising serum potassium levels. Increased plant consumption has also been associated with better metabolic control, reduced inflammation, and improved bowel function in patients undergoing PD. However, randomized controlled trials remain limited, and the effectiveness of such diets in malnourished patients undergoing PD is unclear. Hence, further investigation is required to evaluate the efficacy and safety of a plant-focused diet to inform evidence-based dietary recommendations in this population.

**Objective:**

This study aims to determine the effectiveness of a plant-focused dietary intervention compared with a standard-of-care renal diet on nutritional status, measured by changes in serum albumin, among malnourished patients undergoing PD over 6 months.

**Methods:**

This is an unblinded, open-label, parallel-group randomized controlled trial conducted at a tertiary care hospital in Klang. A total of 100 adult outpatients undergoing PD will be recruited and randomized (1:1) to receive either a plant-focused diet emphasizing plant-based proteins or a standard renal diet emphasizing animal-based proteins for 6 months. Both interventions will be individualized to meet nutrient requirements and delivered through dietitian-led counseling, educational materials, and regular follow-ups. Data will be collected at baseline and after 3 and 6 months of intervention. Parameters assessed include sociodemographic characteristics; anthropometric and biochemical measures (renal, glucose, lipid, and inflammatory profiles); malnutrition inflammation score; dietary adequacy; physical activity and function; quality of life; and knowledge, attitude, and practices of renal diet. Baseline data will be analyzed using descriptive statistics, with independent *t* tests (2-tailed) or Mann-Whitney *U* tests for between-group comparisons. Changes across time points will be analyzed using a generalized linear model for repeated measures, with Bonferroni adjustment for multiple comparisons. Analyses will be adjusted for confounders with significance set at *P*<.05. Ethics approval has been obtained from the Universiti Kebangsaan Malaysia Research Ethics Committee (JEP-2025-812).

**Results:**

This study was funded in 2024 under the *Geran Galakan Penyelidik Muda* (project code: GGPM-2024-051) by Universiti Kebangsaan Malaysia. Participant recruitment began in March 2026, and 9 participants have been recruited as of manuscript submission. Study is expected to be completed by March 2027 Data analysis and manuscript preparation are anticipated to be completed by June 2027.

**Conclusions:**

This randomized controlled trial will provide clinical evidence on the nutritional and safety outcomes of a plant-focused diet in malnourished patients undergoing PD, addressing a major evidence gap in renal nutrition management.

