Recent evidence suggests that plant-based diets may offer benefits for patients undergoing dialysis by reducing blood pressure, metabolic acidosis, and gut-derived uremic toxins without significantly increasing serum potassium levels [13,14]. Nonetheless, concerns remain regarding the safety of these diets in this population, including risks of hyperkalemia, hyperphosphatemia, and inadequate protein or energy intake [15]. Moreover, most existing evidence on plant-focused or plant-based diets is derived from the broader CKD population, with limited data specific to patients undergoing PD. Although observational studies suggest potential advantages, clinical trials investigating the effects of plant-focused diets in patients undergoing PD are lacking, highlighting a significant gap in the current literature that this study aims to address [1]. Additionally, no studies to date have directly compared plant-focused diets with standard renal dietary recommendations in this population. Hence, findings from this study may offer valuable insights to inform future dietary guidelines for PD populations.

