### Research Objectives

The primary objective is to determine the effect of a plant-focused dietary intervention on changes in serum albumin from baseline to 6 months compared with standard-of-care renal diet in malnourished patients undergoing PD.

The secondary objectives are (1) to determine the effect of a plant-focused dietary intervention on changes in anthropometric measurements (BMI, TSF, and MAMC), biochemical and inflammatory markers (lipid profile, hs-CRP, and renal parameters), dietary adequacy and nutrient intake, MIS scores, physical function and muscle strength, QOL, appetite scores, and dialysis adequacy from baseline to 6 months compared with standard-of-care renal diet in malnourished patients undergoing PD and (2) to determine the baseline nutritional status of malnourished patients undergoing PD, including their knowledge, attitude, and practices of renal diet intake, as well as sociodemographic characteristics and medical history.

Exploratory objectives are to assess adherence to a plant-focused dietary intervention over the 6-month period and to evaluate retention rates over 6 months of intervention.

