**Others**									
	Sociodemographic data and medical history	✓		✓					
	Knowledge, attitude, and practices	✓		✓					
	Medication log	✓		✓		✓		✓	
	Quality of life (WHOQOL-BREF^e^)			✓		✓		✓	
	Adverse events report					✓		✓	

^a^MAMC: midarm muscle circumference.

^b^nPCR: normalized protein catabolic ratio.

^c^MIS: malnutrition inflammation score.

^d^SPPB: Short Physical Performance Battery.

^e^WHOQOL-BREF: World Health Organization Quality of Life-BREF.

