### Ethical Considerations

#### Ethics Approval

This study has obtained ethics approval from the Universiti Kebangsaan Malaysia Research Ethics Committee (JEPUKM; JEP-2025-812). The study will be conducted in accordance with the Declaration of Helsinki, Malaysian Good Clinical Practice Guidelines, and institutional policies. Any protocol deviations will be reported to the ethics committee as required. Adverse events will be monitored throughout the study period and followed up as appropriate. Participants will continue to receive standard clinical care throughout the trial.

A data monitoring committee is not required for this study due to the low-risk nature of the intervention. No interim analyses or stopping guidelines are planned due to the nature and duration of the study. Trial conduct will be monitored by the research team to ensure adherence to the study protocol. No formal external monitoring is planned due to the low-risk nature of the study.

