### Literature Gap and Potential Benefits of the Study

While existing studies have focused on the potential benefits of plant-based or plant-focused diets on the broader CKD population, evidence supporting these diets in ESRD populations remains limited, particularly in the PD population. Additionally, concerns remain regarding potential risks, as there is a notable lack of clinical trials, making it difficult to determine the true safety and efficacy of plant-focused or plant-based diets in PD populations [1,15]. This leaves a significant gap in understanding the safety and efficacy of these diets in patients undergoing PD.

This study seeks to address this literature gap by comparing plant-focused dietary approaches with current renal dietary recommendations. Findings of this study will provide clinically relevant evidence on the safety and effectiveness of plant-focused diets in patients undergoing PD and potentially offer insights to guide future dietary recommendations for patients undergoing PD. In addition, publications from this study may potentially encourage better nutrition practices through better nutrition education. Ultimately, this study has the potential to enhance patient-centered care, improve clinical outcomes, and inform policy-level strategies for the nutritional management of ESRD and PD.

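### Safety evidence is promised, but no objective or Table 4 row defines a safety outcome, and serum potassium and phosphate are covered only by a test of means with LOCF

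*Protocol article*

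**What the plan says.** **The claim.** The abstract's Conclusions state: "This randomized controlled trial will provide clinical evidence on the nutritional and safety outcomes of a plant-focused diet in malnourished patients undergoing PD". The Discussion (Literature Gap and Potential Benefits of the Study) says: "Findings of this study will provide clinically relevant evidence on the safety and effectiveness of plant-focused diets in patients undergoing PD". The Research Problem section describes the safety of these diets in peritoneal dialysis as unclear.

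**The risks named.** The Background lists concerns "including risks of hyperkalemia, hyperphosphatemia, and inadequate protein or energy intake".

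**The objectives.** Under Research Objectives, "The primary objective is to determine the effect of a plant-focused dietary intervention on changes in serum albumin from baseline to 6 months". The secondary objectives include renal parameters, dietary adequacy and nutrient intake. The exploratory ones are adherence and retention. None mentions safety, adverse events, serum potassium or serum phosphate, and the same is true of the research questions and hypotheses. The second hypothesis is that the other outcomes improve significantly on the plant-focused diet.

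**The analysis.** Table 4 assigns biochemical data to a repeated-measures model with a time-by-group interaction. The Statistical Analysis text adds LOCF for missing data and significance at P<.05.

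**What is collected.** Table 1 has a renal function test at every visit and a row "Adverse events report" ticked at the post-baseline visits. The Ethics Approval section adds: "Adverse events will be monitored throughout the study period and followed up as appropriate".

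**The concern.** The document promises evidence on two things, nutrition and safety, but turns only the first into objectives, outcomes and analyses. For the two laboratory risks it names, the safety question is how many participants on each diet go above a limit. The stated analysis answers a different question: whether average values change differently between arms, under a hypothesis of improvement. It has no margin, count or interval rule that would make it informative about harm.

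At stake is the weight that the safety statement in the final report can bear. The Discussion expects the findings to help guide dietary recommendations for this population, and safety is one of the main unknowns the trial sets out to address.

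**Working it through.** **1. The plan's own figure.** Sample Size gives SD 5 g/L, difference 3 g/L, two-sided 0.05 and 80% power.

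n = 2 × [5 × (1.96 + 0.84) / 3]² = 43.56, so 44 per arm. With 10% dropout, 44 / 0.9 = 48.9, so 49, which the document rounds to 50. The figure reproduces, but it is an albumin figure. No event rate, margin or potassium SD is given anywhere, so the rates and potassium values below are assumptions. The evaluable number per arm is 50 × 0.9 = 45.

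**2. Power to detect a doubling of a binary safety event, 45 per arm.** With p̄ the mean of the two rates, se0 = √[2p̄(1−p̄)/45] and se1 = √[(p0(1−p0) + p1(1−p1))/45], power = Φ[(p1 − p0 − 1.96·se0)/se1].

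| Assumed rates | se0 | se1 | z | Power | n per arm for 80% |
|---|---|---|---|---|---|
| 5% vs 10% | 0.0555 | 0.0553 | −1.06 | 14.4% | 435 |
| 10% vs 20% | 0.0753 | 0.0745 | −0.64 | 26.2% | 199 |
| 15% vs 30% | 0.0880 | 0.0866 | −0.26 | 39.7% | 121 |
| 20% vs 40% | 0.0966 | 0.0943 | +0.11 | 54.5% | 82 |

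**3. Precision.** With equal rates p in both arms, the 95% half-width of the risk difference is 1.96·√[2p(1−p)/45]: ±9.0, ±12.4, ±14.8 and ±16.5 percentage points at 5%, 10%, 15% and 20%. With no events, the exact two-sided 95% upper limit is 1 − 0.025^(1/45) = 7.9% (7.1% if all 50 are evaluable).

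**4. Means against counts.** For illustration only, take serum potassium as normal with mean 4.2 and SD 0.7 mmol/L in the control arm, and count values above 5.5. These numbers show the arithmetic and are not proposed limits.

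- Control arm: 1 − Φ(1.3/0.7) = 3.2% above.
- Same mean, SD 0.85: 1 − Φ(1.3/0.85) = 6.3% above. The share nearly doubles, and a comparison of means has nothing to detect.
- Mean shifted by 0.2, SD 0.7: 1 − Φ(1.1/0.7) = 5.8% above. A simple two-sample comparison of means has power Φ[0.2/(0.7·√(2/45)) − 1.96] = Φ(−0.605) = 27%.

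**5. LOCF.** Participant Withdrawal and Dropouts allows withdrawal for a clinical condition and retains data up to that point. Scheduled outcome assessments are at months 0, 3 and 6. For someone withdrawn before month 3, the last scheduled value is the baseline one. LOCF then sets month 3 and month 6 equal to baseline, a recorded change of exactly zero, in the participant for whom a change may matter most.

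**The case against.** **Safety is not ignored.** Adverse events are collected and monitored, and renal biochemistry is measured at each visit. One of the named concerns, inadequate protein or energy intake, has a secondary objective and an analysis. The compliance score also applies daily limits to energy, protein, potassium and phosphate intake. All of this stands, so it would be wrong to say that nothing in the plan bears on safety. But the compliance score is a composite of intake and does not count raised serum values.

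**This is a journal article.** Adverse-event tabulations commonly sit in a full protocol or SAP that is not shown. That stands too, and the absence of an adverse-event analysis is not the finding. The finding is a mismatch between things the article does state: its safety claim, its three tiers of objectives, and the analysis that Table 4 assigns to biochemical data.

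**Low power for uncommon events is usual in a trial of 100.** True, and it is not an error in itself. It limits what the safety statement can rest on.

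**Stronger readings that the document does not support.**

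- A reader might infer that a non-significant difference will be reported as proof of safety. No sentence says so; it is a foreseeable risk only.
- A reader might see a contradiction between adverse-event reports at months 3 and 6 in Table 1 and monitoring throughout the study. There is none. Table 1 summarises visits, a report can cover the interval since the last visit, and the inclusion criteria foresee at least monthly phone calls.
- A reader might say that LOCF discards values after a safety withdrawal. It does not. Those values were never recorded, and LOCF fills the gap with an earlier one. An abnormal value seen at month 3 would be carried forward.

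**Conclusion.** The concern holds in this limited form: safety data are collected, but they are not defined as an outcome. For serum potassium and phosphate, the only stated analysis is a superiority-type comparison of means with LOCF, which cannot by itself deliver the promised evidence.

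At the planned size, a doubling of a 5% to 20% event rate would be detected about 14% to 55% of the time, and zero events in 45 would still be compatible with a true rate up to about 7.9%. The power figures rest on assumed rates, a normal approximation and 10% dropout. The exact rates are unknown, but power stays well below 80% across the whole range. The mismatch between claim, objectives and Table 4 needs no assumption. It does not affect the primary albumin analysis.

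**What to change.** Add a safety objective to Research Objectives and a safety row to Table 4. Report by arm:

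- the number and percentage of participants with post-baseline serum potassium, and separately phosphate, above a reporting limit that the investigators prespecify, either shown by baseline status or counted as newly above the limit, so that participants already above it at baseline are handled openly;
- adverse events;
- risk differences with 95% confidence intervals.

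Use observed data without LOCF, and state how many participants in each arm have a post-baseline value, since observed data do not recover what is missing. State that a non-significant difference will not be taken as evidence of safety.

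If the investigators prefer not to add this, limit the statements in the abstract's Conclusions and in the Discussion to descriptive safety data.

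The cost is one further table from laboratory and adverse-event data already planned. With 9 of 100 participants recruited at submission, the outcome can still be fixed before most data exist. The downside is that the intervals will be wide and the safety statement more modest.

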**Trial Registration:**

ClinicalTrials.gov NCT07157397; https://clinicaltrials.gov/study/NCT07157397 and National Medical Research Register NMRR ID-26-00114-LAK; https://nmrr.gov.my/research-directory/d0aad3f4-46ac-4498-8b75-f82f02209cec

**International Registered Report Identifier (IRRID):**

PRR1-10.2196/93558

## Introduction

### Background

According to the Kidney Disease: Improving Global Outcomes guidelines, end-stage renal disease (ESRD) is defined as irreversible kidney failure persisting for more than 3 months [1]. The prevalence of ESRD has significantly increased over the years alongside the growing rates of diabetes and hypertension, both of which are key risk factors for the development and progression of chronic kidney disease (CKD) [2]. ESRD represents the final stage of CKD, in which kidney functions are severely impaired and no longer sufficient to sustain life. As such, renal replacement therapy (RRT) becomes necessary. RRT options include hemodialysis, peritoneal dialysis (PD), and kidney transplantation. However, in Malaysia, due to limitations for organ transplant, dialysis remains the most commonly used mode of RRT [3]. The number of patients requiring RRT in Malaysia has notably increased, with those undergoing PD rising from 13% in 2014 to 18% in 2023, reflecting the growing role of PD in RRT [3].

Despite its benefits, PD is associated with various complications, particularly malnutrition and protein-energy wasting. A systematic review and meta-analysis reported that patients undergoing PD have the highest global prevalence of malnutrition at 45.3%, compared to 43.1% in patients undergoing hemodialysis and 38.5% in nondialysis individuals [4]. The 31st Report of the Malaysian Dialysis and Transplant Registry indicated a widespread malnutrition among patients undergoing PD in Malaysia, with only 27% of patients undergoing PD in half the centers meeting both the recommended body mass index (BMI) and serum albumin targets in 2023 [3]. Additionally, 48% were overweight or obese (BMI≥25 kg/m²), while 8% were underweight (BMI<18.5 kg/m²), highlighting the coexistence of overnutrition and undernutrition [3]. A study conducted among the dialysis population in Malaysia also found a high prevalence of malnutrition among patients undergoing PD, with >70% classified as malnourished across 3 different assessment criteria [5]. Macronutrient and micronutrient deficiencies in patients undergoing PD can result from factors such as inadequate dietary intake, impaired intestinal function, losses through dialysate and urine, metabolic imbalances, chronic inflammation, and the hypercatabolic state of ESRD [6-8]. Poor oral intake is a major contributor to malnutrition among this population. A study conducted in Malaysia reported that the average energy intake among patients undergoing PD ranged from 23 to 25 kcal/kg/day, with protein intake at approximately 0.82 g/kg/day, which are both below recommended levels [9]. Studies have shown that malnutrition in patients undergoing PD result in lower quality of life (QOL) and higher risks of morbidity and mortality [10-12]. Given the strong association between poor nutrition and adverse health outcomes, effective dietary strategies are essential. Therefore, further research is essential to improve nutritional strategies for disease management, ultimately improving patient outcomes and QOL.

Recent evidence suggests that plant-based diets may offer benefits for patients undergoing dialysis by reducing blood pressure, metabolic acidosis, and gut-derived uremic toxins without significantly increasing serum potassium levels [13,14]. Nonetheless, concerns remain regarding the safety of these diets in this population, including risks of hyperkalemia, hyperphosphatemia, and inadequate protein or energy intake [15]. Moreover, most existing evidence on plant-focused or plant-based diets is derived from the broader CKD population, with limited data specific to patients undergoing PD. Although observational studies suggest potential advantages, clinical trials investigating the effects of plant-focused diets in patients undergoing PD are lacking, highlighting a significant gap in the current literature that this study aims to address [1]. Additionally, no studies to date have directly compared plant-focused diets with standard renal dietary recommendations in this population. Hence, findings from this study may offer valuable insights to inform future dietary guidelines for PD populations.

### Research Problem

Malnutrition is highly prevalent among patients undergoing PD [3-5]. Although plant-focused diets have shown potential benefits in reducing mortality, uremia, metabolic acidosis, and inflammation, their safety and effectiveness in patients undergoing PD remain unclear [15]. Limited clinical trial evidence highlights the need for further research to evaluate their impact on nutritional outcomes and overall safety in the PD population [1].

### Research Question

The study is guided by the following research questions:

Does a plant-focused dietary intervention improve nutritional status, measured by changes in serum albumin, compared with a standard renal diet among malnourished patients undergoing PD over 6 months?What is the effect of plant-focused diet in comparison to standard-of-care renal diet on other nutritional outcomes such as anthropometric measurements (BMI, triceps skinfold [TSF], and midarm muscle circumference [MAMC]), biochemical and inflammatory marker (lipid profile, high-sensitivity C-reactive protein [hs-CRP], and renal parameters), dietary intake, malnutrition inflammation score (MIS), assessment of physical function, QOL, appetite, and retention rate in the trial among malnourished patients undergoing PD over 6 months?

### Research Hypotheses

The first alternative hypothesis is as follows: the serum albumin level improved significantly among malnourished patients undergoing PD following a plant-focused diet compared to a standard-of-care renal diet after 6 months of intervention.

The second alternative hypothesis is that other nutritional outcomes, such as anthropometric measurements (BMI, TSF, and MAMC), biochemical and inflammatory marker (lipid profile, hs-CRP, and renal parameters), dietary intake, MIS scores, assessment of physical function, QOL, appetite, and retention rate in the trial, improved significantly among malnourished patients undergoing PD following the plant-focused diet in comparison to a standard-of-care renal diet after 6 months of intervention.

### Research Objectives

The primary objective is to determine the effect of a plant-focused dietary intervention on changes in serum albumin from baseline to 6 months compared with standard-of-care renal diet in malnourished patients undergoing PD.

The secondary objectives are (1) to determine the effect of a plant-focused dietary intervention on changes in anthropometric measurements (BMI, TSF, and MAMC), biochemical and inflammatory markers (lipid profile, hs-CRP, and renal parameters), dietary adequacy and nutrient intake, MIS scores, physical function and muscle strength, QOL, appetite scores, and dialysis adequacy from baseline to 6 months compared with standard-of-care renal diet in malnourished patients undergoing PD and (2) to determine the baseline nutritional status of malnourished patients undergoing PD, including their knowledge, attitude, and practices of renal diet intake, as well as sociodemographic characteristics and medical history.

Exploratory objectives are to assess adherence to a plant-focused dietary intervention over the 6-month period and to evaluate retention rates over 6 months of intervention.

